#### Subgroup

A subgroup analysis will be performed dividing the control groups: one group who received no ECPR and one group who received ECPR after transportation to the hospital. Both therapies in the control group will be compared (using GEE) with the intervention group: prehospital ECPR. Modelling strategy will be the same as described for the primary analysis.

Other a priori defined analytic subgroups are initial cardiac rhythm (shockable vs non-shockable), time to start ECMO flow (< 40 min vs ≥ 40 min) and presence of signs of life during CPR (yes vs no).

Also, historical comparison will be made. Before the ON-SCENE study, dispatch centres were not used to activate the HEMS in an adult cardiac arrest. From the Dutch ARREST database, sequential OHCA patients will be selected who fulfil the ON-SCENE Study inclusion criteria in the timeslot before start of the ON-SCENE study. Patients in which HEMS were activated will be excluded. Hospital mortality will be the primary outcome and secondary the CPC score after 6 and 12 months.

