### Treatment in the intervention group, prehospital ECPR

In the intervention group, HEMS personnel will initiate ECMO cannulation after 20 min of refractory cardiac arrest. The decision to proceed with the cannulation is made solely by the HEMS physician on the basis of the available information regarding the inclusion and exclusion criteria. Since the time it takes for ECMO initiation significantly impacts outcomes, HEMS will collect both the arrival time at the patient location and the time of ECMO flow.

Vascular access will be ascertained through an ultrasound guided puncture of the femoral artery and vein. Insertions of an 25 French venous cannula and a 17 French arterial cannula is performed followed through a Seldinger procedure using an Amplatz Super Stiff™ (with J-tip) guidewire. If they estimated weight is below 50 kg, an 21 French venous and 15 French arterial cannula is inserted(Getinge, Germany). The ECMO machine will then be connected to the cannulas to restore blood flow mechanically, after which chest compressions can be stopped. Target ECMO flow will be between 3 and 4 L per minute and a mean arterial pressure (MAP) of at least 75 mmHg measured with an invasive femoral arterial line placed in the other groin. Arterial blood pressure will be measured using a disposable Compass pressure device (Centurion Medical Products, USA). The ECMO oxygen fraction will initially be set at 0.6 with a standard sweepflow of 2L/min. Ventilation will be maintained at a tidal volume of 4 ml /kg of ideal bodyweight and a respiratory rate of 6 per minute to prevent a rapid decrease in PaCO2. Saturation levels will be measured on the right hand to detect a possible harlequin syndrome. The cannulas will be fixated, and the patient will be transported by ambulance to the nearest hospital providing ECMO care. Standard post-resuscitation care will be provided in the hospital.

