### Statistical consideration

#### Sample size

In the intervention group, the assumption is that ECPR, being initiated within 35 min after onset of cardiac arrest, thereby would result in a hospital survival of 35%. Due to an anticipated learning curve for the HEMS crews, a longer time to cannulation can be expected. The estimation is that this will cause a decrease of survival to 30% in the first 3 months.

In the control group, we assume that 30% of the patients with refractory arrest are transported to the hospital to receive ECPR and that 70% is not transported to an ECPR facility during cardiac arrest. Assumed hospital survival with ECPR in the hospital is 26% (data from Erasmus MC, Rotterdam the Netherlands) and 16% if the patient is not transported to an ECPR facility.

With the different scenarios described above, sample size was calculated using a simulation approach (R package contrast). Anticipating a possible loss of power caused by the stepped wedge design, 175 patients will be included in each study arm to detect the survival difference in mentioned above with 90% power and alpha 0.05. In total 390 patients will be included.

By extrapolating from the Amsterdam ‘ARREST’ database, we estimate that 450 patients in a year of below 50 years will have a witnessed OHCA. Assuming that 25% will fulfil the inclusion criteria, we expect that a maximum of 100 patients a year are eligible for the study. Therefore we assume that a period of 3.5 years should be sufficient to reach the needed number of patients for our study.

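### The comparisons by ECPR received and by time to ECMO flow rest on events after allocation and should be labelled exploratory or descriptive, not left as subgroup effects

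*Protocol article*

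**What the plan says.** Two analyses in the Subgroup section of the protocol article are at issue.

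- **Control split.** The analysis works by "dividing the control groups: one group who received no ECPR and one group who received ECPR after transportation to the hospital". The next sentence reads: "Both therapies in the control group will be compared (using GEE) with the intervention group: prehospital ECPR". The modelling is to follow that of the primary analysis.
- **Flow-time subgroup.** The section continues: "Other a priori defined analytic subgroups are initial cardiac rhythm (shockable vs non-shockable), time to start ECMO flow". The flow-time levels are under 40 minutes and 40 minutes or more. Signs of life during CPR is the third item.

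Four other places bear on this.

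- The Statistical analysis section sets the primary comparison as intention to treat. It gives candidate covariates for the GEE model: age, gender, ambulance arrival time, low-flow time and cardiovascular history. These enter if p < 0.2 between groups.
- The Sample size section says of controls: "we assume that 30% of the patients with refractory arrest are transported to the hospital to receive ECPR and that 70% is not transported" to such a facility during the arrest.
- The control-treatment section makes transport to an ECPR hospital conditional on its being possible.
- The intervention-treatment section says: "HEMS will collect both the arrival time at the patient location and the time of ECMO flow".

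**The concern.** A subgroup analysis estimates a treatment effect when the subgroup is fixed before treatment and can be identified in both arms. Initial rhythm meets that test, and signs of life can too if recorded before cannulation. The two analyses above do not.

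In the control split, a patient enters the in-hospital ECPR part only by staying in arrest and being judged suitable for transport. The part without ECPR mixes patients who regained circulation after 20 minutes with patients who died at the scene. The intervention arm, taken whole, contains all of these types. A difference between it and either control part therefore mixes the effect of the strategy with the way the control part was selected.

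Time to ECMO flow is produced by the intervention or, in controls, by transport and cannulation. Patients never put on ECMO have no value.

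At stake is the reading of two contrasts close to the trial's rationale: on-scene against in-hospital ECPR, and early against late flow. Nothing in the article marks either as descriptive.

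**Working it through.** **Inputs.** All are from the Sample size section unless noted: 30% of controls transported for ECPR with 26% survival; 70% not transported with 16% survival; 35% survival with prehospital ECPR, or 30% in the first 3 months; 175 per arm; 90% power; alpha 0.05 (taken as two-sided). The Discussion cites a mean of 74 minutes from arrest to flow in a Dutch randomised trial of in-hospital ECPR. Table 1 excludes patients expected at a ready ECPR centre less than 30 minutes after collapse.

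**1. The plan's own figure.** Control survival = 0.30 × 0.26 + 0.70 × 0.16 = 0.078 + 0.112 = 0.19.

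n per arm = [1.960 × √(2 × 0.27 × 0.73) + 1.282 × √(0.19 × 0.81 + 0.35 × 0.65)]² / 0.16² = 160, or 172 with continuity correction. If 10% to 20% of intervention patients have the 30% learning-curve survival (an assumed share; none is given), n is 170 to 180 without correction. The stated 175 is consistent with these inputs, so the 19% control rate is a fair reading. The simulation behind it cannot be rerun.

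**2. Who can have a flow time.** Controls with a possible value: at most 0.30 × 175 = 52.5. Controls without: 0.70 × 175 = 122.5. The first is an upper bound because not every transported patient will be cannulated. With half of the stated total of 390 (195 per arm), the figures are 58.5 and 136.5, the same shares.

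For controls who do reach ECMO, expected arrival at a ready centre is 30 minutes or later, which leaves under 40 - 30 = 10 minutes to reach flow in the early level. If the 74-minute mean carried over, few controls would be in that level.

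**3. The control split when the strategy has no effect.** Let both arms have 19% survival, and let the 26% versus 16% gap come wholly from which patients end up in each part.

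- Against controls without ECPR: 19% - 16% = +3 points.
- Against controls with in-hospital ECPR: 19% - 26% = -7 points.

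Rejection probability uses the normal approximation, with s0 the pooled and s1 the unpooled standard error. P = Φ((d - 1.96 s0)/s1) + Φ((-d - 1.96 s0)/s1).

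- 175 vs 122.5, d = 0.03: s0 = 0.0450, s1 = 0.0445, P = 0.095 + 0.004 = about 10%.
- 175 vs 52.5, d = -0.07: s0 = 0.0637, s1 = 0.0674, P = 0.002 + 0.208 = about 21%.

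The nominal level is 5% in each.

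**4. The control split at the design rates.** The whole-arm difference of 35% - 19% = 16 points becomes 35% - 16% = 19 points (power about 96%) and 35% - 26% = 9 points (power about 22%). The contrast with in-hospital ECPR is therefore imprecise as well as confounded.

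**5. Does the planned adjustment help?** None of the named covariates records return of circulation after 20 minutes or the decision to transport, which are what select the control parts. One of them, low-flow time, is what the intervention is meant to shorten.

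**The case against.** - **The article does not say that arms are compared within flow-time levels.** This stands. A reader might infer such a comparison from the listing beside rhythm, but the GEE comparison is stated only for the control split. Early against late flow among ECMO recipients is an equally open reading. What remains is that the listing does not separate a result of treatment from baseline subgroups.
- **The comparator may not be the whole arm.** The wording could mean patients actually cannulated. The intention-to-treat principle makes the whole arm more natural, but the text does not settle it. The other reading does not rescue the analysis, since both sides would then be selected.
- **Immortal-time bias.** A reader might infer this too. The article does not show it: both arms require at least 20 minutes of refractory arrest, the outcome is binary survival at discharge, and no misaligned time origin is evident. The supported problem is selection by treatment received.
- **The figures are planning assumptions.** True. The 70/30 split concerns transport and is not observed data, and the 74 minutes come from another trial. The structural point holds at any substantial share of patients without ECMO.
- **The GEE model adjusts for covariates.** It does, and its list may not be exhaustive, but the named variables miss the selecting events.
- **These are subgroup analyses.** Also true. The primary intention-to-treat comparison does not depend on them, and a reader should not infer that it is affected.

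**Conclusion.** The point holds in this form. The control split compares fractions selected after allocation with an arm that, on the most natural reading, is not selected, and the planned covariates do not remove the selection. The flow-time split cannot support a between-arm effect, because it is a result of treatment and at most about 30% of controls (52 to 53 of 175) can have a value.

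The +3 and -7 points, with rejection near 10% and 21%, are unadjusted and rest on the article's 26%, 16% and 30/70 assumptions, and on that survival gap being entirely selection. If part of the gap is a real benefit of in-hospital ECPR, the bias is smaller. They illustrate the mechanism and do not forecast the trial's error rate.

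The change should be made before analysis. It bears on how secondary results are interpreted, not on the main conclusion.

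**What to change.** 1. State that the comparisons by ECPR received (none, in-hospital, prehospital) are exploratory and non-causal, and say whether the prehospital group is the whole intervention arm or only cannulated patients.
2. Take time to ECMO flow out of the effect-modification subgroups. Report survival by flow time descriptively, among ECMO recipients only.
3. For effect modification by time, use a variable fixed before treatment and available in both arms, with a treatment-by-subgroup interaction on whole arms. Ambulance arrival time is already named in the Statistical analysis section. HEMS arrival time would serve if recorded in both arms; the article mentions its collection only for the intervention group.
4. For on-scene against in-hospital ECPR, whole arms could be compared within strata of expected time to an ECPR centre, provided that the time judged for eligibility is recorded. The article's data list includes neither incident location nor travel time, so a reader should not assume that these are available.

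Items 1 to 3 cost only wording if ambulance arrival time is used. Item 4 may need an added data field. The drawback is that the direct contrast between on-scene and in-hospital ECPR becomes descriptive; on the design rates it had only about 22% power. Patient care and the primary analysis do not change.

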## Methods

### Trial design

This is a nationwide multicentre, prospective, interventional, non-randomised stepped wedge study that evaluates the effect of prehospital ECPR in patients with witnessed OHCA between the age of 18 and 50 years old versus conventional HEMS care without ECPR. The study started end of 2021 and is scheduled to finish by the end of 2025.

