### Eligibility criteria

Patients with a witnessed OHCA between the age of 18 and 50 years old and an initial presentation of ventricular fibrillation/pulseless ventricular tachycardia, as well as pulseless electrical activity with a high suspicion of pulmonary embolism are eligible for inclusion. Detailed inclusion and exclusion criteria are listed in Table 1. The eligibility criteria aim to identify patients with a cardiac arrest that have treatable underlying causes.

**Table 1 Tab1:** Inclusion and exclusion criteria

**Inclusion criteria**	**Exclusion criteria**
Witnessed out of hospital cardiac arrest	ROSC ≤ 20 min
≥ 18 ≤ 50 years (known or estimated)	Expected time from collapse to arrival at an ECPR centre with a direct available ECPR team is less than 30 min.
Initial rhythm of (p)VT /VF or suspected PE	EtCO_2_ et < 1.2 kPa (10 mmHg) during CPR
Refractory cardiac arrest ≥ 20 min ≤ 45 min	No clear ultrasound visualisation of either the femoral artery or the femoral vein.
	**Following initial inclusion, the following patients will be eliminated as soon as the following details are made available**
	Active malignancy
	Cerebral vascular accident < 6 weeks
	Patients with a “do not resuscitate” order, which was not known at time of the arrest

*(p)VT* (pulseless) Ventricular Tachycardia, *VF* Ventricular Fibrillation, *PE* Pulmonary Embolism, *ROSC* Return of Spontaneous Circulation, *ECPR* Extracorporeal Cardiopulmonary Resuscitation, *CPR* Cardiopulmonary Resuscitation, *kPa* Kilopascal

Witnessed arrest is defined as patients who have been last seen well less than 5 min before or show signs of life, meaning extremity movements, normal pupillary reflexes, or gasping during CPR. Whenever the exact age is unknown at the time of care, it is estimated by HEMS. If the patient later on found to be outside the inclusion range of age after cannulation, they will not be excluded.

The time of start of arrest to expected time of arrival at the hospital should be longer that 30 min to be eligible to prehospital ECPR. Furthermore, it should be assumed that the ECPR team would be ready on the ER when the patient arrives. If this is not expected, patient will then receive prehospital ECPR. Only very few patients are so close to the hospital that start of arrest to expected time of arrival hospital is less than 30 min.

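### The historical comparison filters registry patients on the inclusion criteria alone, while trial patients also face prognostic exclusions, so the two groups differ in case mix as well as in period and HEMS attendance

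*Protocol article*

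**What the plan says.** The last paragraph under Subgroup in the protocol article describes a comparison with care before the study. It states four things about the historical group:

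- Source and filter: "From the Dutch ARREST database, sequential OHCA patients will be selected who fulfil the ON-SCENE Study inclusion criteria".
- Period: "in the timeslot before start of the ON-SCENE study".
- Exclusion: "Patients in which HEMS were activated will be excluded".
- Endpoints: "Hospital mortality will be the primary outcome and secondary the CPC score after 6 and 12 months".

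It does not say which trial arm, or whether both arms, will be set against this group.

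Table 1 under Eligibility criteria keeps inclusion and exclusion criteria in separate columns. The exclusions are early ROSC, closeness to an ECPR centre with a team available, end-tidal CO2 below 1.2 kPa during CPR, and "No clear ultrasound visualisation of either the femoral artery or the femoral vein". Patients are also removed after inclusion for active malignancy, a cerebrovascular accident within 6 weeks, or a previously unknown do-not-resuscitate order.

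On geography, Trial design says "This is a nationwide multicentre, prospective, interventional, non-randomised stepped wedge study". The Sample size section derives its recruitment estimate "By extrapolating from the Amsterdam ‘ARREST’ database", while the Subgroup section calls the same registry Dutch.

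**The concern.** A historical comparison is informative only if both groups pass through the same filter. Here the stated rule for the registry names the inclusion criteria and one exclusion that is specific to that group. The trial side has further exclusions, and four of them (low end-tidal CO2, malignancy, recent stroke, do-not-resuscitate order) plausibly mark patients with a poor chance of survival. If such patients stay in the registry group but leave the trial group, the trial side looks better even when neither HEMS nor ECPR has any effect.

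Three other differences come with it. The registry patients are earlier in time. None of them was attended by HEMS, whereas HEMS is dispatched in both trial arms. And the registry may cover only part of the country.

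This is the only planned comparison with care before HEMS was sent to adult arrests. Readers will be drawn to it because the Background states the hypothesis against regular care.

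**Working it through.** **Comparing the filters.** The early-ROSC exclusion mirrors the inclusion criterion of an arrest refractory for at least 20 minutes, so it carries over to the registry. The other Table 1 exclusions have no counterpart among the inclusion criteria. The femoral ultrasound check belongs to on-scene cannulation by HEMS. It could hardly be applied to a group from which every HEMS-activated patient has been removed.

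**Reference survival.** The article gives no figure for the historical comparison, so I use its planning rate for the control arm (Sample size): 30% reach in-hospital ECPR and survive at 26%; 70% do not and survive at 16%.

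0.30 × 26% + 0.70 × 16% = 7.8% + 11.2% = 19.0%

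The planned difference is 35% − 19% = 16 points. As a check on the 19%, a two-sided comparison of 19% with 35% at 90% power needs 160 per arm, or 172 with continuity correction. This is close to the stated 175, which came from a simulation whose settings are not given.

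**Case mix.** Suppose there is no true effect and patients who pass all criteria survive at 19%. Let a share s of registry patients meet a trial exclusion and survive at rate q. Both are assumptions; the documents give neither.

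Registry survival = (1 − s) × 19% + s × q; spurious gain = 19% − registry survival.

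| s | q | Registry survival | Spurious gain (points) |
|---|---|---|---|
| 10% | 5% | 17.1 + 0.5 = 17.6% | 1.4 |
| 10% | 0% | 17.1% | 1.9 |
| 20% | 5% | 15.2 + 1.0 = 16.2% | 2.8 |
| 20% | 0% | 15.2% | 3.8 |
| 30% | 5% | 13.3 + 1.5 = 14.8% | 4.2 |
| 30% | 0% | 13.3% | 5.7 |

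The range is about 1 to 6 points. Widening the assumptions to s = 10-40% and q = 0-10% gives 0.9 to 7.6 points. The sign reverses only if the excludable patients survive better than 19%: at q = 26-30% and s = 10-40% the bias is −0.7 to −4.4 points.

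**Region.** If the share reaching in-hospital ECPR in the registry area were 10% rather than 30%, expected survival would be 0.10 × 26% + 0.90 × 16% = 17%. At 60% it would be 0.60 × 26% + 0.40 × 16% = 22%. The bias then runs from +2 to −3 points, so its direction is open. The 10% and 60% are assumptions.

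**Consequence for a test.** With an assumed 175 patients per group and no true effect, a bias of 2, 4 or 6 points would be declared significant in that direction with probability of about 7%, 17% or 33%. Without bias the figure is 2.5%.

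**The case against.** The best defence is that the article may use inclusion criteria loosely for eligibility. The Sample size section does so when it moves from the share fulfilling the inclusion criteria to the number eligible. On that reading the Table 1 exclusions would be applied to the registry too. This is possible, but Table 1 and the section on treatment in the intervention group treat the two sets as distinct. Even on this reading the ultrasound criterion would probably remain one-sided.

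A second defence is that a condensed article leaves matching, covariates and registry coverage to a fuller document. That is fair for those details, and their absence is not the point here. The selection rule itself is stated, and it is the stated rule that differs from the trial's.

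Four stronger readings are tempting, and the documents do not support them:

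- That one region is certainly being compared with the whole country. The Amsterdam label and the extrapolation make this probable. But the registry is also called Dutch, its coverage is never stated, and the Discussion describes Dutch care as homogeneous.
- That every difference favours the trial. This is plausible for end-tidal CO2 and the later exclusions. It is not established for region or ultrasound. Excluding patients near an ECPR centre could work the other way, although the article says these are very few.
- That trial patients in both arms are fully screened. It is not shown that cannulation-related checks are carried out in the control arm.
- That the trial's treatment effect is confounded by this. That effect comes from the concurrent control arm, which also has HEMS, and the historical comparison does not enter it.

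**Conclusion.** The point holds as a limited one about an ancillary analysis. Followed as written, the registry and trial groups differ in case mix, calendar time and HEMS attendance, and probably in region. The case-mix part would probably flatter the trial side, by about 1 to 6 points against a planned 16. That size rests on three assumptions: comparable patients survive at 19%, 10-30% of registry patients are excludable, and those patients survive at 0-5%. The arithmetic is exact, but the documents supply neither of the last two inputs. The regional part could go either way.

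The choice of trial arm also matters. The section on allocation sends HEMS to the control group precisely to keep HEMS assistance from becoming a second treatment effect. Setting the ECPR arm against patients without HEMS brings that effect back. The correction is worth making before the comparison is run, but the primary analysis does not depend on it.

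**What to change.** - Apply to the registry group every Table 1 inclusion and exclusion criterion that the registry records, and list those that cannot be applied.
- State the registry's coverage. If it is not national, add an analysis limited to trial patients from its catchment area.
- Name the trial arm or arms compared, and say that a comparison with the ECPR arm combines the effects of HEMS attendance and ECPR.
- Adjust for age, initial rhythm and time to ambulance arrival, all of which the article already names as confounders or collected data.
- Report the comparison as descriptive.

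The cost is a little more analysis work and a smaller, less precise historical comparison. Adding screened-out trial-period patients back into the trial side is not recommended. It would need outcomes for people who may not have been followed up, in a study that began at the end of 2021, and it would not be cheap.
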